**C.7.2 Secondary outcomes**

Secondary outcomes include the incidence of intended and unintended (recurring) pregnancies, maternal and infant mortality rates, and the rate of MTCT of HIV among infants born to mothers who acquired HIV during follow-up. Post-partum pregnancies will be diagnosed clinically or by urine testing. Infants of HIV-infected mothers will be tested for HIV by DNA PCR before 18 months of age or by rapid HIV antibody test at >18 months of age.

**C.7.3 Predictor variables**

The primary predictor for Aims 1 and 2 will be treatment assignment. Demographic variables including age, gender, residence, religion, education, number of biological children (live and dead), and occupation will be recorded. Individual mediators: SES will be based on an asset index related to the presence or absence of various household items and commodities[43](#_ENREF_43) that is used regularly in Uganda Demographic Health Surveys and other research studies; health status will be measured using the Karnofsky performance scale. Relational mediators: Partner emotional support: we will adapt one-dimension of the 19-item Medical Outcomes Study (MOS) Social Support Survey[44](#_ENREF_44) that was designed to assess functional social support. This study will only use the emotional/informational support (8 items) dimension of the scale. Partner economic support will be assessed through questions assessing degree of economic dependence. Partner support for health care will be assessed through questions related to material and emotional support specifically related to obstetrical or medical care. Couple communication will be assessed through documentation of HIV serostatus disclosure, knowledge of partner status, and decision-making about current and future pregnancy. Reproductive intentions will be assessed by asking both women and partners about their desire for children within 24 months of the current pregnancy as well as about their past and current use of family planning (FP) methods other than condoms. Unmet need for FP will be calculated as the proportion of women not desiring a child and not using a FP method other than condoms among the total number of women not desiring a child. Vulnerability factors: new partnerships and sexual encounters will be recorded to measure incident exposure. The number of concurrent sexual partners whether casual or stable (> 3 months), history of physical or sexual abuse by the sexual partner or a third party, and alcohol use will be recorded to document high risk behavior.

**C.7.4 Qualitative measurements**

Data collected from focus group discussions and key informant interviews will be triangulated with quantitative data to address: ***(1)*** ***Barriers and facilitators for attending repeat HTC:*** FGDs with women, men and counselors will inform who is and is not attending scheduled HTC and related reasons, as well as the potential limitations of providing retesting and counseling as part of the standard of MCH & PMTCT care services. FGDs will also address potential barriers for service coverage (geographic, cultural, social, financial, educational) and the acceptability and feasibility (from client and counselor perspectives) of retesting women and their partners as well as the potential quality of service women/couples receive.The discussions will address hypothesized structural, relational and individual mediators that may affect re-testing behavior. ***(2) Involving male partners*:** FGDs with women (both individual and in couples), men and health providers will explore issues related to male partners’ roles and involvement in MCH care and HIV prevention. ***(3)*** ***Risk reduction behavior:*** FGDs with women and men will explore what HIV-negative women do to remain negative and the personal, social, economical, cultural and structural facilitators and barriers to different risk reduction options. ***(4)*** ***Unplanned pregnancies at enrolment and during breastfeeding:*** Five women whose pregnancy at enrolment was unintended and five women with an unplanned pregnancy at the end of follow-up in each of the four study arms at each site will be purposively selected and interviewed. Interviews will focus on the circumstances of the unwanted pregnancies in relation to couple communication, risk behavior and HIV prevention.

**C.7.5 Cost data**

Cost data will be collected annually.We will assess costs and cost-efficiency, defined as cost per client served, across all sites and intervention types (individual/couples, WHO repeat HTC/ERHTEC).We will develop a standard cost data collection protocol and manual for gathering expenditure data related to WHO and repeat HTEC in each site. Expenditures will be classified in one of 4 headings: (i) personnel; (ii) recurring goods and services; (iii) capital and equipment; and (iv) building space. In all cases, we will identify costs of providing repeat HTEC and only these costs will be included in the analysis. Capital expenditures such as computers and furniture will be amortized over 5 years of expected useful life, assuming no salvage value. Building space and other in-kind cost will be estimated using the WHO *Cost It* website[45](#_ENREF_45), which provides unit prices by region for many resources, including infrastructure, utilities and professionals’ time. .

**C.8 Statistical considerations and analysis plan**

**C.8.1 Preliminary analyses**

We will characterize the sample and compare treatment groups using descriptive statistics and parametric and non-parametric tests as appropriate. We will also assess differences in dropout rates by treatment assignment and sub-trial, as well as baseline and follow-up correlates of dropout, including interactions with treatment assignment.

**C.8.2 Primary analyses**

The primary analysis of the effect of the intervention on the pre-specified primary outcome will be by intent-to-treat without regard to adherence to the intervention, and will be based on pooled data from the individual and couples trials. We will compare counts of unprotected vaginal sex episodes over the last 3 months reported by each participant, including male partners in the couples trial, using log-link negative binomial models. The reporting period for these counts specified by the follow-up questionnaires will be 3 months at all visits and thus can be ignored. Robust “sandwich” standard errors will be used to account for clustering of repeated outcomes within women and couples; over-dispersion of the outcomes will be captured by the quadratic variance-to-mean parameter of the negative binomial model. To reduce potential bias from dropout, follow-up observations will be weighted by the inverse of the estimated probability of remaining in follow-up, given baseline characteristics, treatment assignment, and post-randomization factors; this approach allows us to account for informative post-randomization variables without adjusting away indirect effects of treatment . The model will allow baseline means to vary by site, sub-trial, participant gender, and visit. However, we hypothesize that the multiplicative effect of treatment on the means will be constant. To protect the type-I error rate, the primary analysis will be conducted and reported under this pre-specified hypothesis, modeling the treatment effect by the interaction of treatment assignment with an indicator for follow-up vs baseline. This assumption was used in the sample size calculation, and will be examined in augmented models allowing for heterogeneity and/or trend in the treatment effect across visits. Site, sub-trial (individual vs couples), and participant gender will be modeled as fixed effects. In secondary analyses, we will assess modification of the treatment effect by these factors, yet power will be limited; results will be reported with confidence intervals.

In calculating STI incidence, time-at-risk will be censored for 14 days following initiation of each STI treatment. Treatment effects on incident STIs will be assessed using logistic models, with robust standard errors to account for clustering within women and couples, and inverse weighting to account for informative dropout. HIV incidence will be modeled using pooled logistic models for internal-censored failures, again with robust standard errors and inverse weighting

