### C.4.6 Randomization

There are four study arms:

| Individual Arm 1 (Arm I-1) | HIV-negative pregnant women enrolling **without** their partner and who will receive standard HIV retesting and counseling in late pregnancy only |
| --- | --- |
| Individual Arm 2 (Arm I-2) | HIV-negative pregnant women enrolling **without** their partner and who will receive the ERHTEC intervention in late pregnancy AND throughout breastfeeding as described below (C.5 Follow-up) |
| Couple Arm 1  (Arm C-1) | HIV-negative pregnant women enrolling **with** their partner and who will receive standard HIV retesting and counseling in late pregnancy only |
| Couple Arm 2 (Arm C-2) | HIV-negative pregnant women enrolling **with** their partner and who will receive the ERHTEC intervention in late pregnancy AND throughout breastfeeding as described below (C.5 Follow-up) |

Enrolled women and couples will be randomized to either the control (repeat HTC in late pregnancy [>36 weeks] only), or to the ERHTEC intervention. Prior to the study onset, four sets of randomized, sequentially numbered lists of participants identification numbers (IDs) will be prepared by the statistician at UCSF. The randomization lists will be computer-generated using random-sized block groups and will include consecutive intervention numbers with corresponding random intervention assignments. Randomization lists will be encrypted in password-protected files, backed up on computer and the UCSF server and emailed to the MU-JHU Data Center in Kampala. Sealed copies of the original randomization list and documentation of the procedure used to generate the lists will be stored in the project administrative offices in San Francisco and Kampala. Each enrolment number will be preceded with a code letter indicating the trial group (“I” for individual, “F” for the female partner of a couple, “M” for the male partner of a couple) and followed by a randomization allocation code (“E” for ERHTEC intervention, “C” for control) and a site code (“KA” for Kampala, “KI” for Kitgum).. At randomization, MU-JHU Data Center will issue randomization numbers to the study coordinators based on the order of enrollment at each site and on the participants’ group allocation (individual or couple).

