## C.5 Follow-up

### C.5.1 Repeat HTC in late pregnancy (>36 weeks)

All women will be given an appointment to be retested and counseled for HIV in late pregnancy as per WHO and Uganda MOH recommendations. Women enrolled at or before the 16th gestational week will be given an appointment for ERHTEC or repeat HTC at 28 weeks of gestation. Women enrolled after the 16th up to the 32nd gestational week will be given an appointment for ERHTEC or repeat HTC at 36 weeks of gestation, or at the first signs of labor, whichever comes first. Women enrolled between the 32nd and 36th gestational week will be given an appointment for ERHTEC or repeat HTC 6 weeks later or at the first signs of labor, whichever comes first. Women enrolled after the 36th gestational week will be given an appointment for repeat HTC at the 6-week post-partum visit to coincide with the first routine immunization visit. In the event that a pregnant woman or couple does not return on the scheduled appointment but presents for delivery, she/they will be retested immediately before or after delivery as per the WHO recommendation. At the late pregnancy retesting visit, all women and men randomized to the intervention arms (Individual and Couple Arms ‘2’) will receive the ERHTEC intervention while women and men randomized to the control arms (Individual and Couple Arms ‘1’) will receive standard HIV retesting and counseling. In addition, both intervention and control women will be bled for syphilis testing and hemoglobin measurement and a vaginal swab will be collected for testing for Gonorrhea/ Chlamydia (G/C), Trichomonas vaginalis (Tv) and the presence of semen (Y chromosome). Symptomatic men will be bled for syphilis testing and asked for a urine sample or urethral swab for G/C and Tv testing. All enrolled women and couples will be asked to answer a follow-up behavioral questionnaire about their sexual and relational behaviors, and reproductive intentions, including family planning. All interviews will be conducted in the language of the participants.

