**C.8.5 Sample size and power**

We will enroll 410 individual women and 410 couples. The combined sample of 1,230 participants will provide 80% power with a type-I error rate of 5% (2-sided) to detect a 10% reduction in the number of unprotected vaginal sex episodes in the repeat HTC arms, net of post-randomization reductions in the control arms. The sample size calculation accounts for within-person and within-couple correlation, estimated at 0.3; a total of 7 assessments, including baseline; 50% cumulative loss to follow-up over 18-months; a control-arm reduction in frequency of 30%; baseline frequency of 5 unprotected episodes per 3 months; and over-dispersion of 2 with respect to a Poisson distribution, used as an approximation to the negative binomial model. To obtain sample size, we modeled the covariance matrix of the parameter estimates in the model used for the primary analysis as the inverse of the sum over participants of matrices X’WX, where X is a matrix of predictor variables specifying time, treatment, and their interaction, with a row for each visit, and W is the inverse of the covariance matrix of the repeated over-dispersed Poisson outcomes, approximated as compound symmetric; for couples, X has two rows per visit. Dropout was accounted for by varying the number of rows of X across participants. This gave an estimate of the SE of the treatment effect estimate, as required in the standard formula for power with a normally-distributed test statistic.

Assumptions above regarding participant retention rate (50%), within-couple correlation (0.3), baseline frequency of unprotected episodes (5 per 3 months), the average reduction in episodes in both arms taken together, and over-dispersion (2), all of which can be estimated without using current information on the treatment effect, will be checked midway through enrolment, i.e. once 50% of the enrolment target has been reached. Power under the planned sample size will then be reviewed using updated estimates for these parameters, under the original assumptions about the treatment effect. If power appears to be low or too high, increasing or decreasing the sample size will be discussed with the study investigators. Because this assessment is made without using current information on the treatment effect, increases or decreases in the sample size can be made with no inflation of the type-I error rate53.54.

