**CONTROLS**

**INTERVENTION**

**- Blood draw + vaginal swab**

**- Baseline questionnaire**

**- STI TC**

**- Blood draw + vaginal swab**

**- Baseline questionnaire**

**- STI TC + Enhanced counseling**

**BASELINE**

**- Blood draw + vaginal swab**

**- Follow-up questionnaire-**

**- Repeat standard HTC**

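### The late-pregnancy count is analysed with the full treatment effect, although its 3-month recall precedes the first ERHTEC session or, if counseling starts at baseline, can reach back before randomization

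*Protocol*

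**What the plan says.** **Model.** C.8.2 compares counts of unprotected vaginal sex over the last 3 months, with one constant multiplicative effect, "modeling the treatment effect by the interaction of treatment assignment with an indicator for follow-up vs baseline". It says the same assumption entered the sample size calculation and that effects varying by visit are examined only in augmented models. On recall it says: "The reporting period for these counts specified by the follow-up questionnaires will be 3 months at all visits and thus can be ignored".

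**Power.** C.8.5 sets the sample: "We will enroll 410 individual women and 410 couples". Its power claim for that sample, pooled over both sub-trials, is: "The combined sample of 1,230 participants will provide 80% power with a type-I error rate of 5% (2-sided) to detect a 10% reduction". The calculation uses 7 assessments including baseline. In the Appendix C summary table these are baseline, late pregnancy, and 3, 6, 12, 18 and 24 months, so late pregnancy counts as follow-up.

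**Start of the intervention, body text.** C.4.6 describes the intervention arms as women "who will receive the ERHTEC intervention in late pregnancy AND throughout breastfeeding as described below". C.5.1 begins the allocation to ERHTEC with "At the late pregnancy retesting visit, all women and men randomized to the intervention arms" and has the follow-up questionnaire completed at that same visit. The abstract and Fig. 1 agree.

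**Start of the intervention, Appendix C.** The baseline entry for the intervention arm, for women and for men, reads "STI TC + Enhanced counseling"; the control entry lacks the counseling. The summary table also marks intervention counseling at baseline.

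**Gap from enrolment to the late-pregnancy visit (C.5.1).** The visit is at week 28 for women enrolled by week 16, and at week 36 or first labor for those enrolled after week 16 and up to week 32. For later enrolments: "Women enrolled between the 32nd and 36th gestational week will be given an appointment for ERHTEC or repeat HTC 6 weeks later", or at first labor if sooner. Women enrolled after week 36 are retested at 6 weeks postpartum.

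**The concern.** A count can show a treatment effect only for the part of its recall window that follows the start of treatment. If the first session takes place at the late-pregnancy visit, the count taken there describes behavior before any intervention. If counseling starts at baseline, a 13-week window still runs back past randomization whenever the visit falls less than 13 weeks after enrolment.

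The single effect term averages this visit with five later ones. It is the follow-up visit with the least dropout, so it carries more weight than any other. The primary estimate is pulled toward no effect, and the 80% power, calculated for the only outcome the trial is powered on, is not delivered.

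**Working it through.** **1. Inputs (C.8.5).** 205 women and 205 couples per arm; mean 5 at baseline and 3.5 in control follow-up (30% reduction); variance 2 × mean; correlation 0.3; 7 assessments; 50% cumulative loss; two-sided 5%; target rate ratio 0.90. The shape of dropout is not given, so several were tried.

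**2. The plan's own figure.** Following C.8.5, the covariance is the inverse of the sum of X'WX on the log scale, with terms for time, treatment and treatment × follow-up, compound symmetry, and two rows per visit for couples.

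Power = Φ(|ln 0.90| / SE − 1.96), with |ln 0.90| = 0.1054.

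- Linear dropout over visits: SE 0.0369; 0.1054/0.0369 − 1.96 = 0.90; power 81.4%.
- Exponential dropout: SE 0.0374; power 80.3%.
- 50% lost by 18 months postpartum: SE 0.0373; power 80.5%.

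The stated 80% reproduces.

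**3. Weight of the late-pregnancy visit.** With linear dropout, retention at the six follow-up visits is 0.92, 0.83, 0.75, 0.67, 0.58 and 0.50, which sums to 4.25. This visit supplies 0.92/4.25 = 22% of follow-up counts.

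**4. Diluted effect.** Let the true log effect be f × ln 0.90 at late pregnancy and ln 0.90 at later visits, and fit the same single-effect model. Results span the three dropout shapes.

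| f | Fitted rate ratio | Power |
|---|---|---|
| 1 | 0.900 | 80-81% |
| 0.75 | 0.906 | 75-76% |
| 0.5 | 0.912-0.913 | 69-70% |
| 0.25 | 0.919-0.920 | 62-64% |
| 0 | 0.925-0.926 | 54-56% |

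Check of the last row, linear dropout: ln 0.9251 = −0.0779; 0.0779/0.0369 − 1.96 = 0.15; Φ = 0.56.

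**5. First reading: ERHTEC starts at the late-pregnancy visit.** Then f = 0 for every participant, whatever the gestational age at enrolment. Power is 54-56%, and about 2,260 participants would be needed for 80%.

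**6. Second reading: counseling starts at baseline.** Here f is the share of a 13-week window that follows enrolment. Gaps from C.5.1, with delivery at week 40 assumed:

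| Enrolled at week | Gap (weeks) | Share after enrolment |
|---|---|---|
| 8 | 20 | 1.00 |
| 16 | 12 | 0.92 |
| 17 | 19 | 1.00 |
| 23 | 13 | 1.00 |
| 28 | 8 | 0.62 |
| 32 | 4 | 0.31 |
| 33 | 6 | 0.46 |
| 36 | 4 | 0.31 |

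Up to week 23 at least 12 of the 13 weeks follow enrolment; after that the overlap with pre-randomization time grows. The protocol does not give gestational age at enrolment, so uniform ranges are assumed. The lower f in each row allows the 2 weeks that C.4.1 permits for completing baseline procedures.

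| Enrolment weeks (assumed) | Mean f | Power |
|---|---|---|
| 8-24 | 0.96-1.00 | 80-81% |
| 12-28 | 0.86-0.94 | 78-80% |
| 12-36 | 0.67-0.77 | 73-77% |
| 20-36 | 0.53-0.66 | 69-74% |
| 24-36 | 0.40-0.55 | 66-72% |

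**7. Possible remedies.** Recoding late pregnancy as a second pre-intervention measurement gives SE 0.0329 (linear) or 0.0336 (exponential). If f = 0, the rate ratio of 0.90 is recovered with power 88-89%. If instead the full effect is already present (f = 1), the same recoding gives a fitted ratio of about 0.938 and power of about 47-48%. Leaving the visit out gives 76-77%.

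**The case against.** A reader might infer that the late-pregnancy count is simply a pre-treatment outcome and that power is therefore well below 80%. The documents do not establish that. Appendix C schedules enhanced counseling at baseline in three places, C.1 describes the intervention as running throughout pregnancy and breastfeeding, and C.4.6 and C.5.1 can be read as describing only the repeat-testing visits. On that reading, power ranges from the planned value to about 14 points below it. Fig. 1 places enrolment at the first ANC visit, and if that is early in pregnancy the loss is negligible. How many women are affected cannot be known without gestational age at enrolment.

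A reader might also take the sentence on the reporting period as the error. It is not: with equal recall length no offset is needed. The operative fault is the follow-up indicator, which ignores where the window falls.

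The dilution is conservative, and the augmented models could reveal a null effect at this visit. Both points stand, but neither restores the primary analysis, which C.8.2 fixes under the constant-effect assumption. Nor would the mid-enrolment review in C.8.5 catch the problem, since it keeps the original treatment-effect assumptions.

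**Conclusion.** The point holds in conditional form. The protocol gives two incompatible starting points for enhanced counseling, and the primary model and power calculation assume a full effect at a visit whose recall window is wholly pre-intervention on one of them and partly pre-randomization for later enrolments on the other.

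On the first, the fitted rate ratio is about 0.925 instead of 0.90 and power is 54-56%. On the second, power is about 66-81%, or 73-77% if enrolment is uniform over weeks 12-36. Type-I error is not affected; the harm is attenuation and lost power.

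These figures assume a 13-week window, an effect proportional to the exposed share of the window, delivery at about week 40, uniform gestational age within each range, and the dropout shapes listed.

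**What to change.** 1. Reconcile the abstract, Fig. 1, C.4.6 and C.5.1 with Appendix C on when enhanced counseling starts. Which is intended is for the sponsor to state.
2. **Only if it starts at the late-pregnancy visit:** in C.8.2, set the follow-up indicator to 1 from the 3-month postpartum visit and use the late-pregnancy count as a second pre-intervention measurement. The reporting-period sentence may then stand as a statement about recall length. This recoding must not be used if counseling starts at baseline, for the loss shown in step 7.
3. **If it starts at baseline:** at the late-pregnancy visit, ask about the time since enrolment, up to 3 months, add a log recall-time offset to the model, and replace the sentence saying the period can be ignored.
4. Restate the power in C.8.5 for the option chosen, giving the assumed distribution of gestational age at enrolment if option 3 applies.

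The cost is protocol wording, one change to the coding or an offset, and under option 3 one questionnaire item. No extra participants or visits are needed for the change itself. Option 3 gives shorter and somewhat noisier counts for late enrollees.
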